#### *Quality control during fieldwork*

Data collection activities during fieldwork will be regularly supervised to ensure that forms are completed correctly. All completed forms will be checked immediately after data collection at the end of each day. The consistency of egg count assessments will be evaluated among the laboratory technicians using standard quality control methods. The laboratory supervisor will read 10% of the slides of each microscopist without prior knowledge of the result. In the case of a discrepancy larger than 10%, a discussion will take place between the laboratory supervisor and the microscopist to resolve the discrepancy and further slides will be examined to avoid repeated errors. The portable scales will be calibrated daily with standard weights, and the measuring mats will be calibrated daily using metal rods of specified lengths. The IIN anthropometrist will conduct two additional training sessions during the study to ensure high validity and reliability of the anthropometric assessments throughout the follow-up period.

### **Analyses**

#### *Primary analysis*

The results of the trial will be analyzed using an intention-to-treat approach. Following description of the study population at baseline, the mean weight gain between the first visit and the last follow-up (at the 24-month visit) will be compared between the four intervention groups using the one-way ANOVA procedure. While randomization should allow for approximately similar occurrence of determinants across the four intervention groups, adjustment for imbalances among the measured determinants and risk factors (e.g. history and duration of exclusive breastfeeding, timing of first introduction of complementary foods, home environment, family structure and characteristics and socioeconomic status) will be performed if needed using multivariate linear regression.

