## **METHODS**

### **Research Design**

The timing, frequency and impact of a deworming intervention, incorporated into health services during routine Growth and Development ('Crecimiento y Desarrollo' or CREDE) visits, will be evaluated in children 12 to 24 months old living in a highly STH-endemic area of the Peruvian

Amazon using a double-blind randomized controlled trial design. There will be four intervention groups randomized to different deworming schedules: 1) usual care and deworming treatment at the 12-month visit and usual care and placebo at the 18-month visit, 2) usual care and placebo at the 12-month visit and usual care and deworming at the 18-month visit; 3) usual care and deworming at the 12-month visit and usual care and deworming at the 18-month visit; and 4) usual care and placebo at both the 12 and 18-month visits. All children will receive deworming at 24 months of age. Weight, length, cognitive and motor development and STH infection will be evaluated at 12, 18 and 24 months of age.

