### **Outcome measurements**

Prior to randomization, a baseline assessment will be conducted which will include anthropometry, and cognitive and motor development. A questionnaire will be administered to the child's mother to obtain socio-demographic information, medical history, feeding practices, and environmental exposure history. Stool specimens will be collected from all children (a small amount of fruit may be given to children, as needed, to facilitate a bowel movement. This method has been used successfully in the past and does not interfere with the quality of the stool). Follow-up assessments will be made at the 18-month CREDE visit, and at the 24-month CREDE visit, at which time all measurements will be repeated.

The primary outcome will be the mean weight gain between the 12 and the 24-month visit. Weight will be measured in duplicate using a portable electronic scale, accurate to the nearest 0.01 kg, calibrated daily using standard weights (Seca 334, Seca Corp., Baltimore, MD, USA).

Additional secondary measurements include length, cognitive and motor development and the prevalence and intensity of STH infections. Length (the recommended measurement of height in children < 30 months of age) will be measured in duplicate as recumbent crown-heel length on a flat surface using a measuring mat (Seca 210, Seca Corp., Baltimore, MD, USA), accurate to the nearest millimetre. Previous studies conducted by the proposed team in the Belén area showed inter and intra-rater reliability of over 95% for length/height and weight assessments (data not published), which are considered acceptable levels for anthropometric measurements. Cognitive and motor development will be assessed using the Bayley scale for cognitive and motor development (Bayley Scales of Infant and Toddler Development, Third Edition. Pearson Education Inc, Texas).

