### **Loss to follow-up**

A 20% rate of attrition has been estimated after 12 months of follow-up. This estimate is based on over eight years of experience in the area which has included follow-up with pregnant women (less than 10 % loss to follow-up over 7 months)  and new mothers (less than 18 % loss to follow-up after 8 months). High participation rates and follow-up will be encouraged by providing reimbursement to cover travel costs (the equivalent of a roundtrip bus ticket) for each of the two follow-up visits (an incentive previously acceptable to both Canadian and Peruvian ethics committees). Mothers have a booklet that they bring to each routine CREDE visit so that essential information can be recorded and the following visit can be scheduled. This should also facilitate the scheduling of the follow-up visits. A higher attrition rate of 20% has been accounted for in the proposed study due to the longer follow-up time of 12 months.

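### The primary ANOVA on 12-to-24-month gain carries an intention-to-treat label but, as written, can use only children weighed at 24 months and leaves the 18-month weight unused

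*Protocol*

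**What the plan says.** The primary analysis section of the Protocol sets the principle: "The results of the trial will be analyzed using an intention-to-treat approach". It then names the variable, "the mean weight gain between the first visit and the last follow-up (at the 24-month visit"), and the test: the groups "will be compared between the four intervention groups using the one-way ANOVA procedure". The outcome section agrees: "The primary outcome will be the mean weight gain between the 12 and the 24-month visit".

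The trial collects more weight data than this analysis uses. Under Research Design, "Weight, length, cognitive and motor development and STH infection will be evaluated at 12, 18 and 24 months of age". Under Outcome measurements, "Follow-up assessments will be made at the 18-month CREDE visit, and at the 24-month CREDE visit, at which time all measurements will be repeated".

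On losses, the Protocol says: "A 20% rate of attrition has been estimated after 12 months of follow-up". The sample size section allows for this loss by raising 366 children per group to 440. The 20% is not divided into loss before and after the 18-month visit.

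**The concern.** An intention-to-treat label suggests that all randomised children count in the comparison. The named variable needs a weight at both ends of the year, so a child not weighed at 24 months drops out of the named test. The words in parentheses tie the last follow-up to 24 months, so carrying an 18-month weight forward is not what is described.

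Some of the lost children will have been weighed at 18 months, and that weight says something about their missing 24-month weight. Leaving it out has two costs:

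- **Precision:** information already collected is not used.
- **Bias:** if late dropout depends on growth up to 18 months, the completers are a selected group, and the ANOVA cannot correct for a weight it does not use.

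The Protocol calls 0.2 kg the smallest meaningful difference, so small shifts deserve attention.

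**Working it through.** **Inputs from the Protocol:** difference 0.2 kg; SD 0.8 kg; four groups with Tukey correction; 80% power; 366 evaluable and 440 randomised per group (1760 in total); 20% loss.

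**Assumed, not in the Protocol:** two-sided familywise alpha 0.05; share q of the loss that falls after 18 months; correlation r between 12–18-month gain and 12–24-month gain; data missing at random given observed weights.

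**Step 1. The plan's own figure.** Pairwise power is taken from the noncentral t distribution with ncp = 0.2 / (0.8 × √(2/n)) and critical value q(0.95; 4, df)/√2 = 2.572. This gives 79.1% at n = 366, and 80% is reached at n = 373. The stated 366 is within 2% of that, so it is reproduced.

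**Step 2. Children available to the ANOVA.** Lost: 0.20 × 440 = 88 per group, or 352 of 1760. Remaining: 440 − 88 = 352 per group. Power at 352 is 77.2%.

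**Step 3. What the 18-month weight adds.** With 80% weighed at 24 months and a fraction 0.8 + 0.2q weighed at 18 months, a likelihood-based model has effective size

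n_eff = 440 / [(1 − r²)/0.8 + r²/(0.8 + 0.2q)].

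For q = 0.5 and r = 0.6: 0.64/0.8 + 0.36/0.9 = 1.20, so n_eff = 440/1.20 = 366.7.

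| Loss after 18 months | r | n_eff per group | Power |
|---|---|---|---|
| none (q = 0) | any | 352 | 77.2% |
| half (q = 0.5) | 0.6 | 366.7 | 79.2% |
| half | 0.7 | 372.3 | 79.9% |
| half | 0.8 | 378.9 | 80.8% |
| all (q = 1) | 0.6 | 379.3 | 80.8% |
| all | 0.8 | 403.7 | 83.6% |

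The simpler approximation 352 + 44r² for the half split gives 368 to 380 and power of 79.4% to 80.9%, the same answer for practical purposes.

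**Step 4. Bias.** Two arms were simulated with a true difference of 0.20 kg. About 11% were lost after 18 months, r was 0.7, and treatment was assumed to shift 18-month gain by 0.2 SD. The probability of loss rose as 18-month gain fell, by the same rule in both arms.

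- Odds ratio 2.7 per SD: completers show about 0.19 kg, so bias is about 0.01 kg.
- Odds ratio 7.4 per SD: completers show about 0.18 kg, so bias is about 0.02 kg.

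A mixed model removes this component, because here the loss depends only on an observed weight.

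**The case against.** **Complete-case analysis is inferred, and missing-data handling belongs in the SAP.** Both parts are fair. No sentence excludes children without a 24-month weight, and a SAP that is not shown could add imputation. The lack of a stated missing-data rule is therefore no finding. What stands is narrower: the Protocol itself selects a variable and test that, unaided, cannot take in a partly observed child.

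**The ANOVA matches the primary outcome and the sample-size method.** True. The proposed model can keep both the outcome and the Tukey comparisons, so this is no reason against it.

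**The 18-month weight cannot rescue the whole 20%.** Correct. A reader might infer that all 88 children per group could be brought back. The weight helps only those lost between 18 and 24 months. A child with a 12-month weight alone enters the model but adds almost nothing about gain.

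**Serious bias is not shown.** A reader might infer that a large part of the treatment effect could be lost. Simulations in which only placebo children with poor early growth leave do turn 0.20 kg into about 0.15 kg (0.13–0.18 kg in a second set). That result rests on selection in one arm, and its size depends on how strong a link is assumed. The Protocol gives no specific mechanism for it: the placebo is identical, all but one of the research team are blinded, and mothers receive stool results only at the end. In addition, Groups 2 and 4 have the same treatment up to 18 months, as do Groups 1 and 3. A common dropout rule based on 18-month gain therefore produces no expected bias within those pairs, given the same relation between early and total gain.

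**The shortfall from 366 to 352 is a separate matter.** It arises because 366 × 1.2 gives 440, whereas 366/0.8 gives 458. It should not be counted here.

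**Conclusion.** The concern holds in a limited form. Under an intention-to-treat label, the Protocol fixes a primary test that, as written, can use about 352 of 440 children per group and makes no use of a weight it already collects. A better method exists for the same data.

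The size is modest. Power for 0.2 kg rises from about 77% to 79–81% if half the loss follows the 18-month visit and r is 0.6–0.8. It does not rise if all loss comes earlier, and reaches about 81–84% if all loss comes later. The avoidable bias is about 0.01–0.02 kg under a dropout mechanism common to the arms. It would be larger only if dropout differed by arm, which the blinded design gives no specific reason to expect.

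The attrition split, the correlation, alpha and the dropout model are all assumptions. The documents do not support saying that the Protocol declares a complete-case analysis, that the full 20% is recoverable, or that a quarter of the effect is likely to be lost.

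**What to change.** Make the primary analysis a mixed model for repeated measures on the 12-, 18- and 24-month weights, with group-by-visit terms, unstructured covariance and adjustment for health centre, the stratification factor. The primary results are the Tukey-adjusted group contrasts at 24 months. Give the 12-month mean a common value across groups, or form the contrast as change from 12 months, so that it still estimates the difference in 12-to-24-month gain. Say which children the intention-to-treat analysis includes. Keep the one-way ANOVA on gain as a sensitivity analysis.

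The cost is a change of wording and slightly more modelling; no new visits, measurements or children are needed. The model assumes that weights are missing at random given those observed. That is an assumption, but a weaker one than the ANOVA on completers makes.

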### **Study population**

The study population will include children attending their routine 12-month CREDE visit (at which time measles vaccination is scheduled) in the study area. Using data provided by the Peruvian Ministry of Health, eight study health centres (“Centros de Salud”) have been identified in high-risk (i.e. high STH prevalence) areas neighbouring Iquitos. These include Centros de Salud: 1) 06 de Octubre, 2) 09 de Octubre, 3) Belén, 4) Cardozo, 5) Bellavista de Nanay, 6) Masusa; 7) 01 de Enero and 8) Fernando Lores.

The inclusion and exclusion criteria for participating children are as follows:

**Inclusion criteria:** 1) children attending any one of the eight study health centres for their 12-month CREDE visit (for feasibility and to ensure recruitment of children from highly STH endemic areas); 2) children living in or near the Belén, Punchana or San Juan district (to ensure recruitment of children from highly STH endemic areas, as well as to ensure high follow-up)

**Exclusion criteria:** 1) children who are attending the clinic for suspected STH infection (as they may require immediate, specific treatment); 2) children who have received deworming treatment

in the six months prior to randomization (as the effect of previous treatment may interfere with the effect of the randomized treatment); 3) parents planning to move outside of the study area within the next 12 months (to maximize participation rates and follow-up); 4) children under 12 months of age (as treatment is not recommended for this age group), or 14 months of age or older (to ensure participants are at a comparable growth and developmental stage); and 5) children with serious congenital or chronic medical conditions and who would be considered by the attending staff not to benefit from deworming.

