#### *Secondary analyses*

Secondary analyses will be conducted to examine differences between groups in terms of derived weight indices (i.e. mean weight-for-age Z score and proportion of underweight), length (mean length gain, length-for-age Z score and proportion of stunting), cognitive and motor development (mean score) and STH prevalence and intensity. Means will be compared using a one-way ANOVA procedure and proportions will be compared using chi-square statistics. Adjustment for imbalances among measured determinants and risk factors will be conducted as needed, using multivariate linear or logistic regression for continuous and dichotomous outcomes, respectively. Length-for-age and weight-for-age Z scores will be calculated using the WHO Anthro software (Version 3, 2009), which compares growth in the study population to a WHO standard population. In addition to age, this method also takes into account the sex of the child. Cut-offs used to categorize the continuous variables of weight, length and eggs per gram are based on WHO standards for underweight (<-2 SD), stunting (<-2 SD) and STH intensity (low and moderate/heavy, according to parasite-specific egg counts), respectively.

To evaluate the possible modification of baseline anthropometry on the effect of deworming, multivariate regression models (e.g. linear for continuous variables and logistic for dichotomous outcomes) will be used with baseline weight and length included as interaction terms. This analysis is included to document the added value of deworming among young children who are already faltering. It will provide insight into both the preventive nature of deworming and also into whether deworming can reverse growth faltering that has already occurred by 12 months of age. Finally, possible intra-cluster correlation (by health centre), will be investigated using the intraclass correlation coefficient. If clustering is indeed detected, hierarchical logistic regression models will be used to obtain accurate estimates of treatment effects.

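### The primary ANOVA of weight gain leaves out baseline weight, sex, entry age and health centre, and the status of any imbalance-triggered adjusted result is unclear

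*Protocol*

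**What the plan says.** **Endpoint and test.** Outcome measurements: "The primary outcome will be the mean weight gain between the 12 and the 24-month visit". Primary analysis: mean gain "will be compared between the four intervention groups using the one-way ANOVA procedure". No covariate is attached to that comparison.

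**Adjustment.** The same section allows for "adjustment for imbalances among the measured determinants and risk factors", which "will be performed if needed using multivariate linear regression". The examples given are "history and duration of exclusive breastfeeding, timing of first introduction of complementary foods, home environment, family structure and characteristics and socioeconomic status". The section gives no criterion for when adjustment is needed, and it does not say which estimate governs if both are produced.

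**Where the omitted variables appear.**
- Baseline weight is measured before allocation: "Prior to randomization, a baseline assessment will be conducted which will include anthropometry". In the analysis plan it enters only the effect-modification models under Secondary analyses, "with baseline weight and length included as interaction terms".
- Age and sex are taken into account only through the Z scores, also under Secondary analyses.
- Entry age runs from 12 months, with children excluded at 14 months: "or 14 months of age or older (to ensure participants are at a comparable growth and developmental stage").
- Randomization and treatment allocation stratifies by health centre. In the analyses, centre is considered only as a possible source of clustering, again under Secondary analyses.

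**The concern.** Covariates in a randomized comparison are best chosen in advance for how well they predict the outcome. Observed baseline imbalances are chance events, so a rule triggered by imbalance selects on the wrong property. Here the examples are feeding, household and socioeconomic factors. The obvious candidates for predicting one-year weight gain (starting weight, sex, exact age) and the stratification factor are not named.

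Two things are at stake. The first is precision: subtracting baseline weight does not remove all correlation between baseline and gain. To the extent that centre predicts gain, an analysis that ignores the stratification also carries a larger standard error than the design warrants. The second is clarity: if an imbalance is seen and a regression is run, a reader cannot tell whether it supplements the ANOVA or takes its place.

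**Working it through.** **Inputs from the protocol (Sample size, Study population).** SD of gain 0.8 kg; difference to detect 0.2 kg; four groups with Tukey-corrected pairwise comparisons; 366 per group, raised to 440 for 20% attrition; expected gain 2.0 kg over 12 months in the double-placebo group; entry age 12 to under 14 months.

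**Assumed, because the protocol gives no figure.** Family-wise two-sided alpha of 0.05; SD of weight at each visit; share of variance explained by covariates (R²).

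**1. The plan's own figure.** The Tukey critical value for a pairwise t statistic with four groups is q/√2 ≈ 2.572. With noncentral t power, 80% needs 373 per group. The stated 366 gives 79.1%, so the figure is reproduced to within 3%. It rests on the unadjusted SD. Attrition of 20% from 440 leaves 440 × 0.8 = 352.

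**2. What baseline weight can add.** With s₁ and s₂ the weight SDs at 12 and 24 months and r their correlation:
- Var(gain) = s₁² + s₂² − 2r·s₁·s₂ = 0.64, which fixes r once s₁ and s₂ are assumed.
- Residual variance after adjusting for baseline weight = s₂²(1 − r²).

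| s₁, s₂ (kg, assumed) | r | residual variance | reduction from 0.64 |
|---|---|---|---|
| 0.9, 0.9 | 0.605 | 0.514 | 19.8% |
| 1.0, 1.0 | 0.680 | 0.538 | 16.0% |
| 1.1, 1.1 | 0.736 | 0.555 | 13.2% |
| 1.2, 1.2 | 0.778 | 0.569 | 11.1% |
| 0.9, 1.1 | 0.697 | 0.622 | 2.8% |
| 1.0, 1.3 | 0.788 | 0.639 | 0.1% |

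If the SD instead grows in proportion to mean weight (assumed 12-month mean 8 to 9.5 kg, s₁ 0.9 to 1.2 kg, mean gain 2.0 kg), the reduction is 0 to 3.3%, and mostly under 1%.

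**3. What entry age can add.** Assume the final visit is scheduled by age, growth is linear at 2.0/12 = 0.167 kg per month, and entry age is uniform over two months. Growth time then varies between 10 and 12 months, so expected gain differs by up to 2 × 0.167 = 0.33 kg between children. The variance is (2²/12) × 0.167² = 0.0093 kg², and 0.0093/0.64 = 1.4%. It is less if most children enter near their first birthday. The documents give no figure for sex or centre.

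**4. Power.** Residual SD = 0.8·√(1 − R²), same Tukey calculation, 352 per group:

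| R² (assumed) | residual SD (kg) | power for 0.2 kg | narrower CI |
|---|---|---|---|
| 0 | 0.800 | 77.2% | – |
| 2% | 0.792 | 78.2% | 1.0% |
| 5% | 0.780 | 79.7% | 2.5% |
| 10% | 0.759 | 82.2% | 5.1% |

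**5. Type I error.** A null simulation used 4 × 352 children, five covariates, R² of 5%, 10% or 30%, and 4,000 runs each. Adjusting mechanically for any covariate imbalanced at p < 0.05 gave 3.6 to 5.0% false positives. Reporting the most favourable of the unadjusted, imbalance-adjusted and fully adjusted results gave 6.1 to 6.9%.

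**The case against.** The best defence is that the primary test is fixed, unbiased under randomization, and the same test that sized the trial. Adjustment sits in a separate conditional sentence and is triggered by baseline imbalance, not by the outcome. A gain score already subtracts baseline weight. The entry window is narrow, and mothers are asked to return on the first birthday. The list of covariates is only illustrative, so it excludes nothing, and its details could sit in a statistical analysis plan. All of this stands, and it limits the point to efficiency and clarity.

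A reader might infer four stronger things that the documents do not support:
- **That the primary model is itself chosen after seeing the data.** The protocol names the ANOVA and nowhere says that an adjusted result replaces it. It is merely silent on the adjusted result's status.
- **That type I error is inflated.** Mechanical adjustment showed no inflation. The 6.1 to 6.9% needs free selection among results, which the protocol does not prescribe.
- **That 11 to 20% of the variance is being lost.** This needs the weight SD to stay constant while mean weight rises by 2.0 kg.
- **That covariate adjustment can never lose precision.** With four arms and one common slope it can. In a contrived case with arm slopes of 0, 0, 0.5 and 0.5 kg per baseline SD, the common slope is 0.25. It adds 0.25² = 0.0625 to the variance in the first two arms, about 10% of 0.64.

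What the defence does not answer is that the protocol itself commits to an imbalance trigger, omits the stratification factor from the primary model, and does not rank the two results.

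**Conclusion.** The point holds as a modest efficiency loss plus an unclear status for the adjusted estimate. It does not make the primary test invalid.

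The size cannot be fixed from the documents. If the weight SD grows with age, baseline weight and entry age together would explain only a few percent, worth roughly one to two and a half power points at 352 per group (R² of 2 to 5%). An R² of 10% would be worth five points, but nothing in the protocol establishes it. The 77% starting value comes from how attrition was allowed for and is not a cost of omitting covariates. Confidence is high on what the protocol says and low on the magnitude.

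**What to change.** In Primary analysis:
- Specify one primary linear model for weight gain (or 24-month weight) with treatment group, baseline weight, sex, age at enrolment and health centre. Keep the Tukey-corrected pairwise comparisons used in Sample size.
- Keep the unadjusted one-way ANOVA as a named sensitivity analysis.
- State that any adjustment prompted by observed imbalance is supportive only and cannot replace the primary result.

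The cost is protocol wording. Anthropometry is taken before randomization, age and sex are needed for the Z scores, and centre is known from the stratification. If the model is not changed, a sentence naming the ANOVA as primary and any adjusted model as supportive would settle the question of status, though not the precision or stratification points.
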